#### Statistical analysis

Categorical data will be summarized by frequencies and percentages, and compared using the chi-squared test. Continuous data will be summarized by mean and standard deviation (normally distributed data) or median and interquartile range (non-normally distributed data), and will be compared using the t-test or ANOVA (normally distributed data) and Mann-Whitney U test or Kruskal-Wallis test (non-normally distributed data), as appropriate. Logistic regression models will be developed to examine the relationship between outcomes and covariates. Survival analysis (e.g., Kaplan-Meier) will be used to study the time-to-event. A two-sided p-value <0.05 will be considered statistically significant.

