## Methods

### Study design

This protocol describes a multicenter, prospective, observational cohort study on diverticular disease. The DDR Trial is open to participation by all tertiary-care hospitals. The DDR Trial aims to investigate short-term postoperative and long-term quality of life outcomes in patients undergoing surgery or medical treatments for diverticular disease. The primary outcome is the quality of life assessment at 12-month in patients with diverticular disease according to the Gastrointestinal Quality of Life index (GIQLI) [19]. The secondary outcome is 30-day postoperative outcomes according to the Clavien-Dindo classification [20].

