#### Patients enrollment

Following patient enrollment, study variables will be collected as patients progress through routine care pathways. Patients’ presentation and treatment may range from mild DD to peritonitis and from non-antibiotic treatment to surgery, respectively. Every patient’s presentations and treatment regimens will be recorded with the appropriate case report forms (CRF).

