### Study variables

The DDR Trial’s variables will include patient baseline, presentation, diagnosis, treatment, and follow-up of patients enrolled, as reported in the CRF. Study variables will be documented for every patient’s presentations and treatments.

Patients enrollment and baseline will be recorded during the first surgical visit, together with a complete clinical examination. In particular, anthropometrics, habits, comorbidity, relevant medications, and baseline quality of life will be collected and categorized (CRF1- CRF2). Charlson comorbidity score adjusted for age will be calculated for every patient [21]. Patients older than 70 years old will be assessed for frailty risk using the modified Frailty Index described by Robinson et al. [22].

Patients and disease presentations are collected according to two different settings (from the emergency room or ambulatory/outpatient clinic). Symptoms, previous presentation, diagnosis, and treatments, need for admission, and treatment will be recorded (CRF3).

Instrumental diagnostic data from colonoscopy, abdominal computerized tomography (CT) and virtual CT colonoscopy be collected (CRF4).

Surgical pre- and intraoperative details will be recorded in the DDR Trial both for emergency procedures and for elective procedures, such as surgical setting, surgical procedure, resection, peritoneal lavage, laparoscopy, operative time, estimated blood loss, conversion, type of mesenteric artery ligation, stapler used and other technical aspects (CRF5). 30-day postoperative complications will be reported and graded according to the Clavien-Dindo classification [20]. Length of stay and post-discharge complications will be evaluated and recorded. Application of Enhanced Recovery After Surgery (ERAS) protocols will be considered valid if only at least 80% of the designed colorectal items will be satisfied [23].

Specimen length, the presence of microscopic and macroscopic abscesses, Crohn’s-like reaction, lymphocyte infiltration, and unknown cancer will be obtained by the pathology report for patients who underwent surgical resection (CRF6).

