Follow-up will be done yearly assessing patient status, time to recurrence, symptoms, medication, consideration of surgical intervention, and quality of life (CRF7). Quality of life will be evaluated according to the Gastrointestinal Quality of Life index (GIQLI) [19]. The GIQLI is a 36-item patient reported outcomes instrument designed to assess GI-specific health-related quality of life in clinical practice and clinical trials of patients with GI disorders. It has five domains (GI symptoms, emotion, physical function, social function and medical treatment) and subscores range from 0–4 while the total score range from 0–144. Higher scores mean better GI health-related quality of life [19]. In addition, Female Sexual Function Index (FSFI) [24], International Consultation on Incontinence Questionnaire (ICIQ) [25], International Index of Erectile Function (IIEF) [26,27], and International Prostate Symptom Score (IPSS) [28], will be used, as appropriate.

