### Data analysis plan

Data analysis will primarily explore the quality of life in patients with DD after different treatments. Secondly, we aim to evaluate surgical management and short-term 30-day postoperative outcomes. We will explore baseline covariants that may identify clinical parameters correlating with favorable outcomes or be predictive of failure in patients undergoing different treatments for DD. Furthermore, we will evaluate recurrence, successive presentations (health utilization), and mortality rates. No personal or hospital-specific comparisons will be performed. The results of the DDR Trial will be reported according to the STROBE statement [31].

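### The tests named for comparing treatment groups assume independent observations and leave no place for hospital, in a multicentre cohort where treatment choice may differ between hospitals

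*Protocol article*

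**What the plan says.** The Study design section states: "This protocol describes a multicenter, prospective, observational cohort study on diverticular disease". It sets no number of centres: "The DDR Trial is open to participation by all tertiary-care hospitals".

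The Data analysis plan section makes quality of life after different treatments the main analysis, with surgical management and 30-day postoperative outcomes second. The Statistical analysis section then names the tools. For categorical data: "Categorical data will be summarized by frequencies and percentages, and compared using the chi-squared test". For continuous data it names the t-test or ANOVA, or the Mann-Whitney U or Kruskal-Wallis test. Logistic regression is to relate outcomes to covariates, and survival analysis is mentioned with Kaplan-Meier as an example. The threshold is: "A two-sided p-value <0.05 will be considered statistically significant".

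The only sentence about hospitals in the analysis is in the Data analysis plan section: "No personal or hospital-specific comparisons will be performed". On repeated records, the Study variables section says: "Study variables will be documented for every patient’s presentations and treatments".

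**The concern.** The main comparison is a continuous score (GIQLI) between non-randomised treatment groups. The tests named for it are the t-test, ANOVA and their rank counterparts. They treat all observations as independent, and in the form named they cannot take a centre term. The only regression named is logistic, which does not suit a continuous GIQLI.

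The article itself gives reasons to expect clustering on both sides of the comparison:

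- **Treatment.** Patients enter through general surgery or gastroenterology units (Study population), so the surgical share may differ by site. The Discussion lists setting and surgeon expertise among the things that decide treatment.
- **Outcome.** Follow-up is an oral questionnaire assessment by the local team (Ethics), so any interviewer effect is also a centre effect.

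When both vary by hospital there are two consequences. The standard error of the treatment difference is too small, so the nominal 5% level is not kept. The difference also mixes treatment with whatever else distinguishes the hospitals that operate more, such as case mix or completeness of follow-up. The first is a variance problem and the second a bias. Leaving hospital out exposes the comparison to both.

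**Working it through.** **Inputs from the article.** Two-sided level 0.05 (critical value 1.960); multicentre design; number of centres open. The article gives no sample size, standard deviation, centre size or ICC, so it has no figure of its own to reproduce. All the inputs below are assumptions.

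**Formulas.** For a treatment difference analysed without regard to centre, with m patients per centre:

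- DEFF = 1 + (m − 1) × ICC(outcome) × ICC(treatment)
- actual level = 2 × [1 − Φ(1.960 / √DEFF)]

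ICC(treatment) measures how far treatment mix differs between centres. It is 0 if treatment is unrelated to centre and −1/(m − 1) if treatment is balanced exactly within every centre.

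**Treatment mix varies between centres (m = 40, so m − 1 = 39).**

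| ICC outcome | ICC treatment | DEFF | Actual level |
|---|---|---|---|
| 0.02 | 0.2 | 1 + 39 × 0.004 = 1.16 | 6.8% |
| 0.05 | 0.2 | 1 + 39 × 0.010 = 1.39 | 9.6% |
| 0.05 | 0.5 | 1 + 39 × 0.025 = 1.98 | 16.3% |

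**Treatment mix does not vary.** With ICC(treatment) = 0, DEFF = 1 and the level is 5.0%. With exact balance within centres, DEFF = 1 − ICC(outcome), which is 0.98 or 0.95, and the level is 4.8% or 4.4%. The test is then neutral or slightly conservative.

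**Check by simulation.** An unadjusted t-test was simulated 4000 times with 20 centres of 50 patients.

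- With treatment ICC about 0.2, it rejected in 7.5% of null runs at outcome ICC 0.02 and 10.7% at 0.05. The formula with m = 50 gives DEFF = 1 + 49 × 0.004 = 1.20 (7.3%) and 1 + 49 × 0.010 = 1.49 (10.8%), in agreement.
- With treatment balanced within centres, it rejected in 4.7% and 4.0%.

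**Repeated records.** If k records per patient with within-patient correlation r were counted as independent, DEFF = 1 + (k − 1) × r. At k = 1.2 and r = 0.3 this is 1.06 (5.7%); at k = 2 and r = 0.8 it is 1.80 (14.4%). This applies only to analyses that use more than one record per patient. It does not touch 12-month GIQLI analysed once per patient.

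**The case against.** The strongest reply is that this is one paragraph in a condensed article. Handling of centre is often left to a fuller plan, and the article nowhere says that centre will be ignored. Part of that stands: a fuller document may deal with it, and nothing here shows that the final analysis will go wrong. But the article is not merely silent. It names the tests for the group comparisons, and as named they have no place for hospital. A stratified chi-squared test or a two-way ANOVA would have one, but the article does not describe either.

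A reader might infer more than the text supports:

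- **That p-values will certainly be too small.** They need not be. The direction depends on whether treatment mix differs between hospitals, which the article makes plausible but does not quantify.
- **That treatment is set wholly by hospital.** This would give far larger errors, but the Discussion describes decisions made case by case.
- **That repeated presentations are counted as separate patients.** The article records every presentation, but it frames the primary outcome as 12-month GIQLI in patients and treats successive presentations as an outcome (health utilization). Nothing plans such pooling.
- **That confidence intervals will be too narrow.** The article mentions none; the point concerns p-values and standard errors.
- **That every named method ignores centre.** The logistic and survival models are described openly enough to hold a centre term.
- **That excluding hospital comparisons settles the matter.** That sentence rules out comparing hospitals with each other. It neither provides for nor forbids adjusting for hospital.

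**Conclusion.** The point holds in conditional form. For the main treatment comparisons, the article fixes tests that assume independence and cannot account for hospital, in a design where its own text makes differences in treatment mix between hospitals plausible. Where such differences exist, the actual level of a nominal 5% test is about 7% to 16%, given 40 patients per centre, outcome ICC 0.02 to 0.05 and treatment ICC 0.2 to 0.5. Where they do not, there is no inflation. Confounding by centre is a further risk that these figures do not measure. Because the direction and size rest on quantities the article does not give, this is a method that should be improved, not a demonstrated error in results.

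**What to change.** Replace the simple tests, for the treatment comparisons only, with regression models that account for centre:

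- **12-month GIQLI:** one value per patient, in a linear model with a centre random intercept or conditioning on centre so that treatments are contrasted within centres. If confounding by centre is the main worry, conditioning is the safer choice, because a random intercept removes it only in part.
- **30-day complications:** the operation as the unit, in a logistic model with centre handled the same way. Restricting to the index presentation would drop operations done at a later one.
- **More than one presentation or operation per patient:** add a patient random effect or use GEE.
- **Few centres:** use a small-sample correction, because plain cluster-robust standard errors are unreliable then, and the number of centres is open.

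State alongside this that centre is adjusted for and that no hospital-level results will be published, so the exclusion of hospital comparisons is respected. The simple tests can stay for describing the cohort.

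The cost is somewhat wider uncertainty and slightly more analysis work. No new data collection should be needed if each record can be traced to its hospital. Data management describes upload by a local investigator for each hospital, which suggests that it can, but the article does not mention a site code, so this should be confirmed.

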## Abstract

**Highlights:**

## Introduction

Diverticular Disease (DD) is defined as clinically significant and symptomatic colonic diverticulosis and includes diverticular bleeding, diverticulitis, and Symptomatic Uncomplicated Diverticular Disease (SUDD) [1]. DD prevalence increases significantly with age, ranging from 10–20% in those younger than 40 years up to 50 to 70% in those older than 70–80 years [2,3]. While diverticulitis occurs in around 5% (1.7% complicated) of patients with diverticulosis [4], admission rate is steadily increasing overall and at a higher rate in younger patients [5]. Indeed, risk factors for DD such as obesity, diet low in fiber, lack of exercise, smoking, and aging of population are increasing. Along with the different clinical presentations and populations affected by DD, diagnosis and treatments have consistently changed. To standardize the treatments, several classifications have been proposed through the years, and several algorithms developed focusing on clinical features and patient’s quality of life more than anatomical and pathological landmarks [1,2,6,7,8]. Moreover, different surgical treatments have been proposed [8,9,10,11,12], while the surgical approach has been shifting to a minimally invasive approach even in the emergency setting [13,14]. Indeed, population, natural history, presentation, severity, and treatment for DD are heterogeneous, and optimal care for patients with DD needs high-quality evidence from large cohort studies [15]. Initial experiences of registry on DD recently appeared in the literature [16,17,18], suggesting the genesis of networks dedicated to DD as the best feasible way to strengthen clinical evidence. However, very few prospective cohort studies explore the outcomes between the different presentations and treatments for DD.

The Diverticular Disease Registry (DDR Trial), on behalf of the Advanced International Mini-Invasive Surgery (AIMS) academy clinical research network, will investigate both short-term 30-day postoperative outcomes and 12-months quality of life assessment in patients with DD. All different surgical and medical treatments will be explored to define the best management for each different presentation of DD. In addition, clinical parameters correlating with favorable outcomes in patients undergoing surgery or medical treatment for DD will be considered according to recurrence, health utilization, and mortality rates.

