## Discussion

Although DD is a common condition, we continue to struggle in defining optimal care as DD is still poorly understood. The primary aim of the DDR Trial is to prospectively collect data on patients with DD, focusing on the clinical presentation, diagnosis, treatments, and clinical follow-up.

Standardizing the data collection of patients with diverticulitis is often tricky for clinical and logistic reasons. Indeed, patients with DD have different healthcare accesses: emergency department, endoscopic unit, surgical, and gastroenterological outpatient departments. Moreover, these patients might be admitted to a surgical or gastroenterological ward. As a consequence, the multiplicity of clinical scenarios results in a lack of accuracy in generating a register that collects clinical data. Herein, we want to pave the way to a collaborative, comprehensive, and user-friendly tool that aims to provide prospective clinical data.

Reaching scientific evidence about medical and surgical treatment of DD is extremely demanding, and it requires considerable resources. Therefore, high-quality evidence is limited, and frequently recommendations have low levels of evidence. Moreover, the decision-making process for DD treatment is determined on a case-by-case basis according to the different clinical presentations, settings, surgeon expertise, and patient preferences [15]. In addition, the decision for elective surgery for SUDD or smouldering diverticular disease (SDD) truly belongs to a clinical grey zone that needs to be clarified. Overall, because these clinical nuances are frequently present in daily practice and so hardly intelligible, it becomes clear the need for a structured outcome-related prospective registry. Indeed, follow-up data for patients with SUDD o SDD, either after surgical or conservative treatments, will provide high-quality evidence for management recommendations and practical decision making.

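### The 12-month GIQLI is to be compared across non-randomised treatments, but the only fitting methods named are unadjusted tests, and the one regression named (logistic) does not suit the score.

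*Protocol article*

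**What the plan says.** All places are in the protocol article.

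- **Outcome.** Under Study design: "The primary outcome is the quality of life assessment at 12-month in patients with diverticular disease", measured by the GIQLI. Study variables gives the scale: "subscores range from 0–4 while the total score range from 0–144". No cut-off or responder definition is stated.
- **Aim.** The Introduction says: "All different surgical and medical treatments will be explored to define the best management for each different presentation of DD". The Data analysis plan says: "Data analysis will primarily explore the quality of life in patients with DD after different treatments". The Conclusions expect the study to help identify optimal care.
- **Methods.** Under Statistical analysis, continuous data "will be compared using the t-test or ANOVA (normally distributed data) and Mann-Whitney U test or Kruskal-Wallis test", with significance at two-sided p<0.05. The same paragraph adds: "Logistic regression models will be developed to examine the relationship between outcomes and covariates". No linear model, ANCOVA or propensity method is named.
- **How patients come to a treatment.** The study is observational. The Discussion says that the treatment decision "is determined on a case-by-case basis according to the different clinical presentations, settings, surgeon expertise, and patient preferences".
- **Data available.** Under Study variables, "baseline quality of life will be collected and categorized", alongside comorbidity (age-adjusted Charlson score), emergency or outpatient setting, symptoms, and previous presentations and treatments.

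**The concern.** The section names methods by type of data, and the GIQLI total is continuous, so the rule for continuous data is the one that reaches the primary outcome. None of the four tests in that rule carries a covariate. The article also describes the mechanism that makes an unadjusted contrast misleading: patients reach surgery or medical care because of features that can themselves affect later quality of life.

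Logistic regression does not close the gap. It needs a categorical outcome, and none is defined for the GIQLI. The Data analysis plan gives baseline covariates a prognostic role, finding what goes with success or failure. It does not give them the role of making treatment groups comparable.

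At stake is whether the primary result can be interpreted. A larger cohort does not help, because it only estimates the confounded difference more precisely. The conclusions the authors hope for, on best management and optimal care, need a comparison that at least accounts for measured case mix.

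**Working it through.** The article gives no SD, sample size, effect size or treatment shares, so there is no figure of its own to reproduce. The numbers below are illustrations on assumed inputs and show how the size of the bias depends on them.

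**1. Which named method fits the outcome?**

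| Method named | Fits a 0–144 score? | Carries covariates as named? |
|---|---|---|
| t-test, ANOVA, Mann-Whitney, Kruskal-Wallis | yes | no |
| Logistic regression | no, without a cut-off | yes |
| Chi-squared test; Kaplan-Meier | no | no |

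No named method both fits the score and adjusts the treatment comparison.

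**2. Bias of an unadjusted contrast that spans presentations.** Assume no true treatment effect, two equally common presentations A and B, operated shares p_A and p_B, and a gap of d points in mean 12-month GIQLI between A and B.

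- Share of A among operated patients = p_A/(p_A + p_B)
- Share of A among the others = (1 − p_A)/[(1 − p_A) + (1 − p_B)]
- Absolute bias = d × (difference of the two shares)

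With 60% versus 10% operated: 0.6/0.7 = 0.857 and 0.4/1.3 = 0.308, difference 0.549. For d = 10 to 15 the bias is 5.5 to 8.2 points.

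With SD 22 in each group and 100 patients per group, SE = 22 × √(2/100) = 3.11. The ratios are 5.5/3.11 = 1.77 and 8.2/3.11 = 2.65, so the chance of exceeding 1.96 is about 0.42 to 0.75. If 22 is instead the SD within a presentation, it is 0.41 to 0.72.

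With 50% versus 20% operated: 0.5/0.7 = 0.714 and 0.5/1.3 = 0.385, difference 0.330. The bias is 3.3 to 5.0 points, with rejection in about 18% to 36%.

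With equal operated shares the two shares of A coincide and the bias is 0.

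**3. Simulation on different assumptions.** No true effect, SD 20 within presentation, half of patients with the more severe presentation, which lowers the score by 5, 10 or 15 points; total N of 200, 500 or 1,000; 2,000 simulated studies per setting.

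| Operated, severe vs mild | Spurious difference (5/10/15-point gap) | Rejection, unadjusted t-test |
|---|---|---|
| 50% vs 50% | 0 / 0 / 0 | 0.043–0.054 |
| 50% vs 30% | −1.0 / −2.1 / −3.1 | 0.07 (gap 5, N 200) to 0.59 (gap 15, N 1,000) |
| 60% vs 20% | −2.1 / −4.2 / −6.2 | 0.12 (gap 5, N 200) to 0.99 (gap 15, N 1,000) |

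A linear model with treatment and presentation rejected in 0.039 to 0.062 over all 27 settings (nominal 0.05). In this simulation presentation is the only confounder, which the registry cannot count on.

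**4. Within a single presentation.** Stratifying removes the bias in steps 2 and 3 but not the rest. If treatment groups within one presentation differ by 10 points in baseline GIQLI, and baseline and 12-month scores correlate at 0.5 with equal SDs (all assumed), a difference of 0.5 × 10 = 5 points remains at 12 months with no treatment effect.

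**The case against.** The strongest reply is that the Statistical analysis paragraph is a generic list by data type for a whole registry. It does not assign the t-test or ANOVA to a named primary comparison. The article condenses a fuller protocol, and an analysis plan may exist. The Discussion describes the primary aim as collecting data, the Data analysis plan speaks of exploring, and reporting is to follow STROBE.

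Part of this stands. The adjustment set, the interaction term and any propensity analysis may properly sit elsewhere, and their absence from an article is no fault. What the article does state is a different matter: it names its methods, and none that adjusts is suited to its primary outcome. An exploratory tone does not remove confounding when a significance threshold is set and optimal care is the stated destination.

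Three stronger readings are tempting and are not supported:

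- *Presentations will be pooled.* Nothing says so. The Introduction points to analysis by presentation, and the statistical section is silent. The pooled figures above are therefore illustrations only.
- *A confounded difference will be reported as a treatment effect.* That predicts the authors' conduct; the document does not state it.
- *No covariate enters any treatment analysis.* The logistic sentence excludes no outcome, and treatment could be a term in such a model. The supportable statement is that this model type does not fit the score as defined.

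It is also fair that covariate adjustment is incomplete. Two of the selection factors named in the Discussion, surgeon expertise and patient preference, would remain uncontrolled.

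**Conclusion.** The point holds in a limited form. For a continuous primary outcome compared across treatments that were chosen and not randomised, the article names only unadjusted tests and one regression type that does not suit the score. Differences obtained that way mix case selection with treatment, within a presentation as well as across presentations, and cannot carry conclusions on best management. The per-presentation aim is stated in the Introduction but does not reach the analysis.

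The size is not known. The 5.5–8.2 points and 42–75% false positives rest wholly on the assumed SD, group size, operated shares, gap between presentations and a pooled contrast. Other assumptions gave 1.0 to 6.2 points, and equal shares gave none. Inflation of the false-positive rate follows whenever a factor affects both treatment choice and 12-month GIQLI and its effects are not offset by those of other factors. This is a cheap improvement, best made before the data are analysed.

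**What to change.** Revise the Statistical analysis section as follows:

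- Make the main treatment comparison a linear (ANCOVA) model of 12-month GIQLI on treatment strategy. Adjust for continuous baseline GIQLI (the score itself, not a categorised version), presentation and severity, emergency or outpatient setting, previous episodes, age and Charlson score.
- Report treatment contrasts within each presentation, only where both strategies are actually used.
- Keep the t-test, ANOVA, Mann-Whitney and Kruskal-Wallis comparisons as descriptive.
- Word conclusions as adjusted associations, and state that confounding by surgeon expertise and patient preference remains.

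**Cost.** A few sentences and modest extra analysis. Study variables already lists baseline quality of life, presentation, setting, previous presentations and comorbidity; the sponsor should confirm that the baseline instrument is the GIQLI.

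**Downsides.** Presentations in which treatments do not overlap can only be described. A baseline GIQLI taken during an acute episode may partly reflect that episode, so setting belongs in the model and the result should be checked separately in emergency and outpatient patients.

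### The only covariate model named is logistic regression, so the plan gives no route to an adjusted difference in points on the 0–144 GIQLI primary outcome

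*Protocol article*

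**What the plan says.** All references are to the protocol article.

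- **Primary outcome (Study design):** "The primary outcome is the quality of life assessment at 12-month in patients with diverticular disease according to the Gastrointestinal Quality of Life index". Study variables gives the scale: "subscores range from 0–4 while the total score range from 0–144".
- **Secondary outcome (Study design):** "The secondary outcome is 30-day postoperative outcomes according to the Clavien-Dindo classification".
- **Unadjusted comparisons (Statistical analysis):** continuous data are summarised by mean and SD or by median and IQR. They are compared by t-test or ANOVA if normal, and by Mann-Whitney or Kruskal-Wallis if not.
- **Covariate models (Statistical analysis):** "Logistic regression models will be developed to examine the relationship between outcomes and covariates". No other regression is named. Kaplan-Meier is given as an example for time-to-event data.
- **Purpose (Data analysis plan, Introduction):** the first aim is quality of life after different treatments, and the registry is meant to establish the best management for each presentation. The plan also looks for baseline predictors of a good outcome or of failure, and defines neither term.
- **How treatment is chosen (Discussion):** individually, according to presentation, setting, the surgeon's expertise and the patient's preference.

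**The concern.** The stated covariate model does not match the stated primary endpoint. Binary logistic regression needs a yes/no outcome, GIQLI is in effect continuous, and the article gives no threshold that would turn one into the other.

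This matters more here than in a randomised trial. Patients treated surgically and medically will differ in severity, presentation and baseline quality of life, because those features drive the choice of treatment. A crude t-test or rank test on 12-month GIQLI mixes the effect of treatment with the reasons for giving it. The adjusted model is the one that readers will rely on.

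Followed as written, with logistic regression in its usual binary sense, the section offers two routes: an unadjusted comparison on the full scale, or an adjusted odds ratio at an unstated cut. The second discards information, leaves the cut open to choice after the data are seen, and does not tell a clinician how many GIQLI points separate the treatments.

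**Working it through.** The article gives no sample size, power, GIQLI standard deviation or cut-off, so there is no stated figure to reproduce. The check has two parts.

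**1. Which named method can do what with 12-month GIQLI**

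| Named method | Keeps the full score? | Adjusts for covariates? | Result in GIQLI points? |
|---|---|---|---|
| t-test / ANOVA | yes | no | yes, crude |
| Mann-Whitney / Kruskal-Wallis | ranks only | no | no |
| Logistic regression (binary) | no, needs a cut | yes | no, odds ratio |
| Kaplan-Meier | not applicable | no | no |

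No row both adjusts and gives a result in points.

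**2. What a cut would cost (illustration)**

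Assumptions, none of them from the article: normally distributed scores, two equal groups, two-sided α = 0.05 (this one is the article's), 80% power, and standardised differences d of 0.2, 0.3 and 0.5.

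*Information kept.* For a small shift, splitting a normal score so that a proportion p lies on one side keeps φ(z_p)² / [p(1−p)] of the information, where φ is the standard normal density and z_p its p-quantile.

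- p = 0.5: 0.3989² / 0.25 = 0.637
- p = 0.3: 0.3477² / 0.21 = 0.576
- p = 0.2: 0.2800² / 0.16 = 0.490

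So 1,000 patients analysed with a cut would be worth about 640 (median split) down to 490 (20/80 split) analysed on the full scale.

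*Sample size and power.* On the full scale, n per group = 2(1.960 + 0.842)² / d². For the cut score, n comes from the usual two-proportion formula. The cut is placed midway between the group means, so the proportions above it are 1 − Φ(d/2) and Φ(d/2).

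| d | n per group, full score | Proportions above the cut | n per group, cut score | Ratio | Power of cut score at the full-score n |
|---|---|---|---|---|---|
| 0.2 | 393 | 0.460 v 0.540 | 618 | 1.57 | 61% |
| 0.3 | 175 | 0.440 v 0.560 | 275 | 1.57 | 61% |
| 0.5 | 63 | 0.401 v 0.599 | 100 | 1.59 | 60% |

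A central cut is the favourable case. If only 20% of the reference group lies above the cut, the required n per group rises to 758, 329 and 115, and power at the full-score n falls to 52%, 53% and 55%.

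**The case against.** The strongest reply is that the score is not mishandled at all. The section has an explicit rule for continuous data, GIQLI falls under it uncut, and those tests serve the stated aim of exploring quality of life after different treatments. The logistic sentence also has natural targets in death, recurrence and treatment failure. A further model for GIQLI may stand in an analysis plan that is not shown, and the article nowhere says that logistic regression is the only model allowed.

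Much of this stands. It confines the problem to the covariate models and rules out any claim that the sponsor intends to dichotomise GIQLI. It does not remove the problem. The tests that keep the score whole are unadjusted, and the Discussion itself explains why unadjusted comparisons will be confounded. Nor is the point mere silence: the sentence states a method and applies it to outcomes without distinction, and in its usual form that method does not fit the primary one.

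A reader might infer three stronger things that the text does not support:

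- **That Clavien-Dindo grades must be collapsed.** The article does not say binary. Proportional-odds regression is a logistic model and takes the grades as they stand. It could in principle take the GIQLI total uncut too, but would give an odds ratio, not points.
- **That baseline GIQLI will be modelled in bands.** Study variables says that "baseline quality of life will be collected and categorized", but this closes a list of baseline items and may mean only that they are grouped on the forms. No classes are given.
- **That this wording shows how the 12-month score will be treated.** It concerns baseline only.

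**Conclusion.** The concern holds in a limited form. The article handles GIQLI on its full scale only in unadjusted tests. The one covariate model that it names, read in the usual binary sense, cannot be applied to GIQLI without an undefined cut-off. In a cohort where treatment is chosen by indication, that leaves no named route to an adjusted GIQLI difference in points.

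If the gap were filled by cutting the score, the information kept would be about 64% at the median, 58% at 30/70 and 49% at 20/80. A comparison with 80% power on the full scale would have about 60% with a central cut. These losses rest on assumed normality and assumed effect sizes. They show the cost of one way of following the text, not a loss known to be planned. The mismatch should be corrected, and it is easily corrected.

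**What to change.** In Statistical analysis, state that:

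- 12-month GIQLI is compared between treatments by linear regression (ANCOVA), adjusted for baseline GIQLI as a continuous covariate, for disease presentation and for the other baseline confounders already on the case report forms;
- the result is reported as an adjusted mean difference in points with a 95% confidence interval, and the t-test, ANOVA and rank tests are descriptive and unadjusted;
- logistic regression is kept for binary or ordinal outcomes, saying which form is used. For Clavien-Dindo grade, ordinal logistic regression is already compatible with the present wording;
- any GIQLI cut-off, if one is wanted as a supportive analysis, is fixed and justified before the data are analysed.

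Also confirm that the raw baseline GIQLI score is stored in the database, not only a category. If it is, the cost is wording alone: no new data, visits or patients. If it is not, data capture must be changed for patients still to be enrolled, and the baseline adjustment is limited for those already in.
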